#### 8.3.1 Weight

**Time of day:** Because the weight of an individual varies during the day, weight will be measured at the same time of day on each follow up visit. With patients being recruited throughout the day, enrolment in the study and the first weight measured will be at any time on day-0.

To limit intra-day variation in weight, efforts will be made to ensure follow-up visits are scheduled at the same time of the day throughout the 6 month study follow-up. A weighing within 3 hours on either side of the original weighing will be accepted. If a patient arrives outside this limit, the participant will be asked to return the next day within the proper time window.

**Weighing procedures:** Two weighing scales, both SECA model 835, a very precise electronic scale, will be used for small babies and toddlers sitting or standing on the scale. Below weights of 20 kg the scale has a precision of +/-20 grams and for heavier weights up to 50 kg a precision of +/-50 grams. To minimize inaccuracy due to a child's movement, great care will be taken to place the scale level and on a stable surface and every effort will be made to ensure that restless children are kept calm during the weighing procedure. Quality control measures will be taken to ensure scale accuracy and the scales will be checked daily by a constant weight of 10Kg.

The weighing will be done by the same team of two (three) persons throughout the study, monitored and supervised closely by the field research coordinator (FRC). All children will be weighed undressed and without jewellery or other ornaments. One person will perform the weighing (ensuring scale is correctly positioned, correctly calibrated, and assisting the guardian with placing the child on the scale). The weight will be taken when the child is relatively still. This same person will read out loud the weight measured. The second person will visually observe the weight on the digital scale to confirm that it has been correctly read out loud and the second person will verbally repeat the weight and record the confirmed result on the appropriate form.

#### 8.3.2 Height

In order to detect even small increases in the height of a child, height will be measured at day-0 and every monthly visit to the clinic. Two (three) persons will use a precision height board (infant-child-adult measuring board, aluminium, Promes). One person will read out loud the height measured and the second person will verbally repeat the height for confirmation and record the result on the appropriate form.

### **8.3.3 MUAC**

MUAC will be measured using an standard MUAC tape at day 0 and at the monthly visits. One person will read out loud the MUAC measurement and the second person will verbally repeat the measurement and record the result on the appropriate form.

### **8.3.4 Oedemas**

Oedema will be evaluated applying pressure with thumb to top part of the foot for three seconds. If an oedema exists, an imprint will be left on the part of the foot where pressure was applied. The oedema must be observed on both feet, legs or could be generalised (always bilateral oedema) for considering the child has nutritional oedema. Oedema will be evaluated at day 0 and at monthly visits.

## **8.4 Three study diseases**

Three diseases/morbidities are targeted during this study: malaria, diarrhoea, and LRTI. Clinical diagnoses will be made using existing standard MSF/WHO protocols and case definitions [26,27] A flow chart with to guide diagnosis and inclusion is detailed in Annex f7-diagnostics.doc.

- **Diarrhoea:**

The forms of diarrhoea include:

1. Acute diarrhoea, simple without blood: the passage of at least three liquid stools per day for less than 2 weeks
2. Persistent/chronic diarrhoea: diarrhoea beginning at least 14 days ago, and any period without diarrhoea has not exceeded two days. (WHO definition) [28]
3. Bloody diarrhoea

- **Lower Respiratory Tract Infection (LRTI)**

Refers to acute pneumonia:

- children presenting with cough or difficulty breathing **plus**
- Increased respiratory rate
  - Age 6–11 months: RR > 50 breaths /minute
  - Age 12 to 59 months: RR > 40 breaths /minute

- **Malaria, Plasmodium falciparum and other species**

- Fever or history of fever within 24 hours with positive malaria RDT result

## **8.5 Compliance**

Compliance regarding the consumption and acceptability of the nutritional supplements will be assessed only after the first 14 days of supplementation, through a questionnaire and collection of returned supplement sachets (used or unopened). The study dispenser will count and record the returned sachets (empty or unopened) after the questionnaire is completed.

## **8.6 Emergency unblinding procedures**

Only when a serious adverse event occurs and it is deemed necessary to unblind a patient's intervention group will that patient's allocation be revealed.

## **8.7 Withdrawal procedures**

Children will be withdrawn from the study if:

- i.) Participant fulfils criteria for acute malnutrition during follow-up period.
- ii.) There is a serious protocol violation
- iii.) Participant is erroneously included
- iv.) There is the risk that the nutritional supplement would negatively influence a prescribed medical protocol (i.e. medical treatment has priority).

Patients who become acute malnourished will be referred to MoH/Action Against Hunger (AAH) Supplementary and Therapeutic Feeding Program for care and treatment.

Participants who are withdrawn from the study will continue to be followed up if possible and monitored following standard study protocol. The use of data for analysis from withdrawn participants will be assessed by the study statistician.

## **8.8 Endpoints**

### **8.8.1 Primary endpoint**

The primary endpoint is “negative nutritional outcome (NNO)” of a child within the 6 months follow-up period. The incidence of a negative nutritional outcome will be defined according to the baseline nutritional status.

- i) for children with no malnourishment at time of entry into study, “negative nutritional outcome” is defined as progression to moderate or severe malnourishment

Thus, the event of a child reaching a “negative nutritional outcome” at least once within 6 months of follow-up period will be compared between the three study groups.

### **8.8.2 Secondary endpoints**

Secondary endpoints include

- Number of NNO's per study group in a period of 6 months
- Time to NNO
- Number of new events of a study disease in 6 months
- Weight change at 14 days and 28 days after study inclusion, and at end of study period
- Rate of weight change (grams/kg/day) at 14 days and 28 days after study inclusion, and at end of study period
- Proportion of children not gaining weight (including losing weight), measured at day-14 and day-28 after study inclusion.
- Proportion of children developing bilateral oedema
- Mortality: overall mortality, including the three study diseases and malnutrition.
- Morbidity, including the three diseases.
- Proportion of children with a reported cough at clinical visit

## **8.9 Data collection**

An overview of forms where data are recorded is given in annex f10-overview data flow. Data will be routinely captured using EpiData software program, including double data entry to ensure quality data capturing.

Data will be routinely sent to the MSF Study PI and epidemiologist based in Barcelona for routine quality control. To minimise missing data during the trial, the database will be checked routinely. Any critical data missing will be obtained by questioning staff and, if necessary, the guardian.

Minimize bias must be done through training and supervision. Staff during all the study will be selected for the same responsibilities.

In an effort to minimise missing data, participants will be reminded of their scheduled visit 24 hours prior to the scheduled visit by means of mobile telephone. If a patient misses an appointment, the participant will be traced by outreach workers to ensure follow-up. When possible, information on the reason for missing data will be recorded.

Study data will be kept on the study site and handled confidentially. After study completion, all records will be stored in an appropriate manner at MSF offices at capital level for long-term storage. All data (paper records and electronic data) will remain the property of MSF-OCBA, who will commit to retain the data for 5 years.

MoH OPD patient medical cards will remain the property of the patient and/or health facility, as per current standard procedures in the routine health services.

## **9. DATA ANALYSIS**

## **9.1 Sample size\***

The sample size is based on the primary hypothesis: Supplementation for 14 days with RUTF, concurrent to appropriate medical treatment for malaria, and/or LRTI, and/or diarrhoea reduces the incidence of malnutrition.

The sample size calculation is based on a combined incidence of moderate and severe malnutrition amongst children who are sick.

There are hardly studies reporting the incidence of malnutrition and no studies reporting incidence of malnutrition among sick children. Therefore for the purpose of these calculations, we assume that the incidence is estimated by dividing the prevalence of malnutrition by the period of having malnutrition times 6 months:  $= [(Prevalence / Duration\ of\ moderate\ malnutrition) * 6\ months]$

The estimated incidence for moderate and for severe malnutrition will be added to result in the incidence of negative outcome as defined as primary endpoint of this study.

The prevalence of moderate malnutrition among sick children is 15.5% and the prevalence of severely malnutrition among sick children is 7.2% according to the results if we take the survey done by MSF-OCA at February 2009.

Literature gives a duration of malnutrition (untreated) is estimated to be 7.5 months [29] and the duration of severe malnutrition is estimated at 4 months at the time of the survey. As duration of malnutrition might be different in the context of Karamoja we varied assumptions in order to use the lowest incidence as a basis for the sample size. This results in sample size that is large enough to give enough statistical power for the primary hypothesis (the sample size increases with a decreasing incidence). Increasing the prevalence of malnutrition in general or decreasing the duration of severe malnutrition (as there is treatment available) resulted in a higher incidence, but prolonging the duration of moderate malnutrition to 10 months gives a lower incidence.

Therefore the incidence is based on duration of 4 months for severe malnutrition and duration of 10 months for moderate malnutrition.

This results in an incidence of 0.201 per 6 months

Formula:  $0.201 = [(0.155 / 10 + 0.072 / 4)] * 6$

The assumed incidence rate in the control group (baseline incidence) is 0.20. A 30% reduction in the supplementation group, which is considered a clinically and operationally relevant improvement, results in an assumed incidence rate of 0.14 in each of the two interventions groups.

A Poisson regression with a binary independent group variable with proportion of 0.5 (equal allocation ratio) using a sample of 1320 observations (i.e. 660 per group) achieves 80% power at a 0.05 significance level to detect a incidence rate ratio of at least 0.7 (i.e. incidence rates of 0.14 (intervention rate) vs. 0.2 (baseline rate)).

To account for an assumed drop-out rate of approximately 10%, 734 children will be included in each group (i.e. 2202 in total for all three groups).

The sample size estimation is based on the first two hierarchical test hypotheses (while the third hypothesis comparing RUTF with MNP for non-inferiority is considered explorative). Sample size estimations are performed with PASS 2008 (Version 08.0.13, Windows XP) and SAS version 9.2 (SAS Institute, Cary, NC, USA).

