#### **9.3.1 Primary analysis of the primary endpoint**

The primary endpoint is “negative nutritional outcome” of a child within the 6 months follow-up period as defined in section 8.8.1. The incidence rate (in formulae below referred to simply as ‘rate’) of “negative nutritional outcome” will be computed as the number of events divided by total observed person-time in each treatment group. As an “event” the first time a child reaches a negative nutritional outcome will be used. The primary analysis of the primary endpoint will be performed on the intention to treat population with no imputation of missing data.

In the primary analysis, RUTF will be compared to the control group.  
The hypotheses in this step are

$$\begin{aligned} H_0: \text{rate}_{\text{RUTF}} &= \text{rate}_{\text{Control}} \\ \text{vs.} \\ H_1: \text{rate}_{\text{RUTF}} &\neq \text{rate}_{\text{Control}} \end{aligned}$$

where  $\text{rate}_{\text{RUTF}}$  = rate of “negative nutritional outcome” in the children in the RUTF group, and  $\text{rate}_{\text{Control}}$  = rate of “negative nutritional outcome” in the children in the control group.

The comparison of rates among the treatment groups will be performed by a Poisson regression model, adjusted for nutritional status at enrolment (fixed effect) and will be performed within one model including the three intervention groups with contrasts for each two-group comparison. Tests will be two-sided with a significance level of 0.05.

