#### **9.3.2 Secondary analysis of the primary endpoint**

Although the study is primarily powered for the comparison between the RUTF and control group the other groups will be compared as well, keeping in mind that the sample size might not be large enough to obtain significant results.

Since there are three interventional groups to be compared, a hierarchical test procedure will be used to account for multiplicity.

1) In a first step, RUTF will be compared to the control group, which is described above as analysis of primary outcome

If the RUTF group is not significantly different at a 0.05 level (two-sided test), the hierarchical procedure is stopped (all following analyses will be considered explorative). If the RUTF group is significantly different at a 0.05 level, the hierarchical procedure is continued with step 2.

2) In the second step, MNP will be compared to the control group.  
The hypotheses in this step are

$$H_0: \text{rate}_{\text{MNP}} = \text{rate}_{\text{Control}}$$

vs.

$$H_1: \text{rate}_{\text{MNP}} \neq \text{rate}_{\text{Control}}$$

where  $\text{rate}_{\text{MNP}}$ =rate of “negative nutritional outcome” in the children in the MNP group, and  $\text{rate}_{\text{Control}}$ =rate of “negative nutritional outcome” in the children in the placebo to MNP group.

If the treatment factor is not significant at a 0.05 level (two-sided test), the hierarchical procedure is stopped (all following analyses will be considered explorative). If the treatment factor is significant at a 0.05 level, the hierarchical procedure is continued with step 3.

3) In the third step, RUTF will be compared to MNP (non-inferiority test).  
The hypotheses in this step are

$$H_0: \text{rate}_{\text{RUTF}} - \text{rate}_{\text{MNP}} > -\square$$

vs.

$$H_1: \text{rate}_{\text{RUTF}} - \text{rate}_{\text{MNP}} \leq -\square$$

where  $\text{rate}_{\text{RUTF}}$ =rate of “negative nutritional outcome” in the children in the RUTF group,  $\text{rate}_{\text{MNP}}$ =rate of “negative nutritional outcome” in the children in the MNP group, and  $\square$ =inferiority margin.

As non-inferiority margin, a  $\square$  of 2% will be used (i.e. allowing a slightly worse result in the MNP compared to the RUTF group). The third step will be tested at a 0.025 level (one-sided test), by a one-sided 97.5% confidence interval of the difference in rates between the RUTF and the MNP group.

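### RUTF v MNP non-inferiority is exploratory without condition in section 9.1 but a gated formal step of the hierarchy in section 9.3.2, so the status of an MNP non-inferiority result is fixed two ways

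*Protocol*

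**What the plan says.** Section 9.1 (Sample size) states: "The sample size estimation is based on the first two hierarchical test hypotheses". It then sets the third comparison apart, "while the third hypothesis comparing RUTF with MNP for non-inferiority is considered explorative". No condition is attached to that label.

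Section 9.3.2 (Secondary analysis of the primary endpoint) says that "a hierarchical test procedure will be used to account for multiplicity". The order is RUTF v control, MNP v control, then RUTF v MNP. The gate into the last step reads: "If the treatment factor is significant at a 0.05 level, the hierarchical procedure is continued with step 3". The step has its own level and interval: "The third step will be tested at a 0.025 level (one-sided test), by a one-sided 97.5% confidence interval". It also has a fixed margin of 2%, explained as tolerating an MNP result a little worse than RUTF. In that section the exploratory label appears only where an earlier step fails: "the hierarchical procedure is stopped (all following analyses will be considered explorative").

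Section 9.3.1 defines the rate being compared as "computed as the number of events divided by total observed person-time in each treatment group". The margin in 9.3.2 carries no time unit.

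**The concern.** The two sections answer the same question differently: if RUTF and MNP each beat control, is the RUTF v MNP test part of the formal inference or not? Section 9.1 says no in every case. Section 9.3.2 gives the test everything a formal step has (a place in the multiplicity procedure, a gate, a level and a margin) and calls later steps exploratory only after a failure. Nothing in the protocol says which section governs. This is not detail left to the SAP, because the protocol itself gives both answers.

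What is at stake is the conclusion about MNP as a substitute for RUTF. Section 2 lists RUTF v MNP under the secondary objectives. Section 1.5 describes RUTF as costly and bulky and asks whether its macronutrient part is essential. With the status open, a success could be reported as an established finding or as a hint, and the choice could be made after the result is known. A failure could be taken to show that macronutrients are needed, although the trial is far too small for that inference.

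**Working it through.** **1. The two texts in each scenario**

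| Outcome of steps 1 and 2 | Status of RUTF v MNP in 9.1 | Status in 9.3.2 |
|---|---|---|
| Step 1 fails | exploratory | exploratory |
| Step 1 succeeds, step 2 fails | exploratory | exploratory |
| Both succeed | exploratory | tested as step 3, one-sided 0.025, 2% margin |

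The sections agree in the first two rows and part in the third, the only one in which step 3 is reached. The one-sided 0.025 level and the one-sided 97.5% interval match each other. The conflict is about status, not alpha.

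**2. The plan's own sample size**

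Inputs from section 9.1: control rate 0.20 and active rate 0.14 per 6 months, rate ratio 0.7, equal allocation, 0.05 (taken as two-sided, as in 9.3.1), 80% power. The Signorini formula for Poisson regression gives

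N = [1.96·√4 + 0.8416·√(2 + 2/0.7)]² / [0.20·(ln 0.7)²] = (3.920 + 1.855)² / 0.02544 ≈ 1,311.

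The protocol states 1,320, and power at 1,320 is 80.3%. Dropout: 660/0.9 = 733.3, rounded up to 734. The stated size is therefore reproduced for RUTF v control and for MNP v control.

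**3. Power of a conventional non-inferiority test for MNP at that size**

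Assumptions: both active rates 0.14 (section 9.1), 660 per group, margin read as 0.02 per child per 6 months, one-sided 0.025.

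- Poisson variance: SE = √(2·0.14/660) = 0.0206. Power = Φ(0.02/0.0206 − 1.96) = Φ(−0.99) ≈ 16%.
- Binomial variance: SE = √(2·0.14·0.86/660) = 0.0191. Power = Φ(0.02/0.0191 − 1.96) = Φ(−0.91) ≈ 18%.
- The confidence limit lies 1.96·SE from the estimate: 0.040 (Poisson) or 0.037 (binomial), about twice the margin. On the Poisson scale MNP would have to be observed about 0.040 − 0.020 = 0.020 better than RUTF to pass.
- With 734 per group, power is 17% to 20%. With both active rates at 0.20, it is 13% to 15% at 660 per group.
- Size for 80% power, Poisson: 2·0.14·(1.96 + 0.8416)²/0.02² ≈ 5,495 per group. Binomial: 4,726 per group.

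**4. How often step 3 would be reached**

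A simulation under the protocol's rates (660 per group, Wald tests) gives about 63% for passing steps 1 and 2 together and about 8% for passing all three. The Wald test gives about 75% power for step 1, a little below the planning formula, so these figures are approximate. Under the planning assumptions, the scenario in which the sections disagree is more likely than not.

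**5. The printed hypotheses**

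The alternative in step 3 is that the RUTF rate minus the MNP rate is at or below minus the margin. The event is a bad outcome, so this says MNP is worse than RUTF by at least the margin. Non-inferiority of MNP is the opposite statement, that the difference lies above minus the margin, and it is printed as the null. The power figures in item 3 are for the conventional test, not for the hypotheses as printed.

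**The case against.** The strongest reply is that the texts can be reconciled. Section 9.3.2 never uses the word confirmatory. Its exploratory clause says what happens after a failure; strictly, it does not say that step 3 is formal otherwise. Section 9.1 refers to the hierarchical hypotheses in the same sentence, so its author had the hierarchy in view, and the remark may mean only that the trial was not sized for step 3. It is true that the formal status is inferred. But that reading does not explain why a test that is always exploratory sits inside a procedure adopted for multiplicity, behind a gate, with a level and margin of its own.

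Other objections stand and limit the point:

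- A reader might infer that the false-positive rate is inflated. It is not: step 3 is last in a fixed sequence, so its label leaves steps 1 and 2, and the primary analysis, unchanged.
- Low power is not hidden. Section 9.3.2 warns that the sample may be too small for comparisons other than RUTF v control, though it gives no figure.
- The cost-effectiveness question in section 1.5 is mainly whether micronutrients alone prevent malnutrition. That is step 2, which is unaffected. Only the question whether macronutrients are essential bears on step 3.
- A reader might infer from the missing time unit that the margin could mean almost anything. The documents do not support that. Section 9.1 works per 6 months and the endpoint is defined over 6 months. A monthly reading would allow 6·0.02 = 0.12, putting MNP at 0.14 + 0.12 = 0.26, above the 0.20 assumed for controls. That is not a slightly worse result.

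**Conclusion.** The point holds as an unresolved conflict over the status of one secondary comparison. It arises only when steps 1 and 2 both succeed, about 63% of the time under the protocol's rates. It affects what may be claimed about MNP replacing RUTF, not error control and not the primary result.

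The sample size favours the label in section 9.1. A conventional non-inferiority test at a 0.02 margin has about 16% (Poisson) to 18% (binomial) power, so with equal supplements it would fail about 82% to 84% of the time. That rests on active rates of 0.14, 660 per group and the 6-month reading of the margin. It would be too strong to say that the test almost always fails, and no passage states that a failure would be read as showing RUTF better. That is a misreading to guard against, not one the plan makes. The reversed hypotheses in step 3 need correcting whichever status is chosen.

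**What to change.** In section 9.3.2:

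1. End the formal hierarchy after step 2 and label RUTF v MNP exploratory, in line with 9.1.
2. Report the rate difference with its two-sided 95% confidence interval. The limit of interest is the same as that of the one-sided 97.5% interval already planned.
3. State the margin on the protocol's own scale, 0.02 per child per 6 months.
4. Reverse the printed hypotheses, so that the null is MNP worse by at least the margin and the alternative is MNP worse by less than the margin or not worse.
5. Add one sentence giving the power (about 16% to 18% under the planning rates) and saying that failure to show non-inferiority is not evidence that RUTF is better.

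The SAP should carry the same wording. No data collection, patient procedure or sample size changes. The cost is that the sponsor gives up a formal non-inferiority claim that it was unlikely to reach.
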